## Abstract

**Background:**

Both pulmonary and mental health are affected following hospitalization for COVID-19 pneumonia. Pulmonary rehabilitation therapy has demonstrated benefits in improving mental health, but no validated combined programs that include mental health have been proposed.

**Objective:**

This article presents the design of a trial that aimed to assess whether the participation in a combined rehabilitation program that includes home-based respiratory physiotherapy and telephone-based psychological support is associated with a greater improvement of pulmonary and mental health outcomes 7-12 weeks after COVID-19 hospitalization discharge compared with posthospital usual care provided by a public Peruvian hospital.

**Methods:**

WAYRA (the word for air in the Quechua language) was an open-label, unblinded, two-arm randomized controlled trial. We recruited 108 participants aged 18-75 years who were discharged from the hospital after COVID-19 pneumonia that required >6 liters/minute of supplemental oxygen during treatment. Participants were randomly assigned at a 1:1 ratio to receive the combined rehabilitation program or usual posthospital care provided by a public Peruvian hospital. The intervention consisted of 12 at-home respiratory rehabilitation sessions and 6 telephone-based psychological sessions. The primary outcome was the 6-minute walk distance. Secondary outcomes included lung function, mental health status (depression, anxiety, and trauma), and quality of life. Outcomes were assessed at baseline (before randomization) and at 7 and 12 weeks after hospital discharge to assess the difference between arms.

**Results:**

This study was funded by the Peruvian National Council of Science Technology and Technology Innovation in July 2020. Ethics approval was obtained on September 2, 2020. Recruitment and data collection occurred between October 2020 and June 2021. Results are expected to be published by the end of 2022.

**Conclusions:**

WAYRA was the first randomized controlled trial evaluating combined pulmonary-mental health rehabilitation for hospitalized COVID-19 survivors in resource-limited settings, potentially providing a foundation for the cost-effective scale-up of similar multidisciplinary rehabilitation programs.

**Trial Registration:**

ClinicalTrials.gov NCT04649736; https://clinicaltrials.gov/ct2/show/NCT04649736

**International Registered Report Identifier (IRRID):**

RR1-10.2196/36001

## Introduction

The COVID-19 pandemic is resulting in millions of survivors with long-term complications [1]. Complications are more frequent in patients who required hospitalization, affecting both physical and mental health [1]. Systematic reviews show that 24% to 36% and 40% to 58% of patients with COVID-19 report dyspnea and fatigue after acute illness, respectively [2,3]. The frequency of depression and anxiety in COVID-19 survivors ranges from 12% to 15% and 13% to 22%, respectively [2-5].

Although recommendations for post-COVID-19 rehabilitation already exist [6-9], the evidence is scarce from different aspects. First, most studies have focused on pulmonary rehabilitation [10-12], but no study has evaluated a rehabilitation program that integrates a psychological component. The high frequency of mental illness suggests that patients may benefit from physiological support. Second, no published clinical trial has evaluated a home-based rehabilitation program, an approach that could have advantages over inpatient programs and comparable efficacy [12]. After hospitalization, COVID-19 patients could have several health limitations that make it difficult to visit health care facilities for rehabilitation. Third, most strategies to address the sequelae of COVID-19 have been developed in high-income countries and therefore do not consider some of the challenges specific to developing countries, such as the availability and quality of professionals and infrastructure to carry out rehabilitation [13].

Considering that COVID-19 is a disease that results in short-, medium-, and long-term physical and mental impairment, and that limited rehabilitation strategies have been evaluated, this protocol describes the design and methodology of a randomized controlled trial that aimed to evaluate the effects of integrated home-based respiratory physiotherapy combined with a telephone-based psychological intervention on pulmonary and mental health–related outcomes at 7 and 12 weeks after hospital discharge in patients with COVID-19 pneumonia. The primary objective of the trial was to compare 6-minute walking distances at 7 and 12 weeks after hospital discharge among participants in a combined program versus those who received usual posthospital care provided by a Peruvian public hospital.

## Methods

### Study Design

WAYRA (the word for air in the Quechua language) was a randomized, controlled, open-label, two-arm clinical trial that evaluated the efficacy of a 6-week home-based respiratory physiotherapy and telephone-based psychological program compared to usual posthospital care provided by a public Peruvian hospital, aimed at improving exercise tolerance, lung function, mental health, and quality of life (QoL) outcomes. A baseline assessment was conducted at hospital discharge, with two follow-ups at week 7 and 12 (Figure 1). Due to the nature of the rehabilitation interventions, blinding of participants and the researchers was not possible; however, the data scientist conducting the data analysis was blinded. The trial was registered at ClinicalTrials.gov (NCT04649736).

**Figure 1 figure1:**
[figure not shown]
Expected study enrollment and timeline diagram. 6MWT: 6-minute walk test.

### Study Setting and Population

This study took place in the COVID-19 ward at Hospital Nacional Cayetano Heredia (HNCH), a public tertiary-care hospital and a major referral center that serves approximately 3 million people from underserved neighborhoods in the northern metropolitan area of Lima, the capital of Peru. HNCH has been one of the main COVID-19 national referral centers throughout the pandemic, with 241 hospitalization beds and 23 intensive care unit beds [14]. During the pandemic, more than half of Lima’s population reported depressive symptoms, with increased rates of symptoms reported among young people with low income and without higher education [15].

The study population consisted of confirmed cases of COVID-19, diagnosed by serological or molecular tests, including members of both sexes, between 18 and 75 years of age, discharged from hospitalization, who received high-flow oxygen (>6 liters/minute) treatment at any point during hospitalization. Participants with prior respiratory pathology or psychiatric diagnoses were excluded. The complete eligibility criteria are provided in Textbox 1.

Inclusion and exclusion criteria.
**Inclusion criteria**
Age between 18 and 75 yearsDischarged from hospitalization with a confirmed COVID-19 diagnosisCapable of understanding study proceduresCapable of providing informed consentRequired oxygen flow >6 liters/minute or through a high-flow device at any time during hospitalizationEvaluated by the rehabilitation service at least once during hospitalization
**Exclusion criteria**
Contraindications to the 6-minute walk testContraindications to spirometryComplications during the baseline 6-minute walk testNeurological pathology, neuropathy, limb dysfunction, or other underlying physical disability that makes physical exercise impossiblePregnant or breastfeedingNo access to the internet or a telephone lineHistory or existing lung diseases such as asthma, chronic obstructive pulmonary disease, fibrosis, or tuberculosisModerate or severe heart disease (Grade III or IV, New York Heart Association)Diagnosed with another severe disease in the last 6 monthsSevere depression or suicidal ideationTaking any medication for depression and/or anxiety, or another medication prescribed by a psychiatrist before the onset of COVID-19Cognitive impairment or sensory disturbance

### Enrollment

A trained nurse made the initial contact and prescreening, starting with a daily review of the list of hospitalized patients during the enrollment period, to identify potentially eligible participants among newly discharged patients or those close to discharge in the following days. Potential participants were informed about the study and its procedures and were invited to participate. Those who accepted received a detailed explanation of the nature of the study, randomization, study procedures, their potential risks and benefits, their rights as participants, and the study timelines. Potential subjects were explicitly told that participation was not mandatory, that there was no penalty for refusing to participate, and that their clinical treatment at the hospital would not be compromised in any way if they refuse to participate or opt out of the study at any time. All interested patients received the screening informed consent form (Multimedia Appendix 1) for their review, and they provided a signature once all their questions and concerns were addressed.

After obtaining participant consent and signature, a trained nurse performed the screening assessments, including review of eligibility criteria compliance and baseline measurements. These included cognitive status (assessed using the Montreal Cognitive Assessment, visual impairment version [MoCA-BLIND] [16]), sociodemographic and clinical data, baseline respiratory symptoms (using the St. George’s Respiratory Questionnaire [SGRQ]), depressive symptoms (using the Nine-Item Patient Health Questionnaire [PHQ-9]), anxiety symptoms (using the Generalized Anxiety Disorder Assessment [GAD-7]), posttraumatic stress disorder symptoms (Impact of Event Scale-Revised [IES-R]), and QoL (using the 36-Item Short Form Survey [SF-36] and EuroQuol-5D [EQ-5D]). Subsequently, a trained physician assessed the participants’ exercise tolerance with the 6-minute walk test (6MWT) and pulmonary function with a spirometry test. Participants were screened for severe depressive symptoms. Those with a GAD-7 score ≥15 or IES-R score ≥37 were referred to a psychiatrist for evaluation and treatment. Participants with a PHQ-9 score ≥20 and self-reported suicidal ideation during the psychological evaluation were immediately referred to mental health services for treatment and were excluded from the study. Patients who completed the baseline assessments and met eligibility criteria were enrolled into the study. The recruitment team communicated with the study coordinator who performed a baseline data quality verification, the allocation to one of two arms (control or intervention), and assigned a participant ID code.

### Randomization

We used a blinded list preuploaded in REDcap [17], which was created by a data administrator who was not involved in study recruitment. To achieve balance in the number of participants assigned to each study arm, the treatment arm was randomized at a 1:1 ratio using permuted blocks of variable size, randomly varying from 2, 4, and 6 participants. The blocks were randomized using the Stata v16.0 *ralloc* command (StataCorp). Finally, all participants were scheduled for follow-up visits as described in Table 1. Sample selection and enrollment took place between the day before hospital discharge and up to 3 days after discharge.

**Table 1 table1:** Data collection schedule.

Time point				Study period (week)																											
				Enrollment (–1)		Baseline (0)		Postallocation																							Close-out (12)
								1		2		3		4		5		6		7		8		9		10		11			
**Enrollment**																															
	Informed consent		✓																												
	Eligibility screen		✓																												
	Allocation				✓																										
**Interventions**																															
	**Intervention arm**																														
		Home-based respiratory rehabilitation					✓		✓		✓		✓		✓		✓														
		Telephone psychological support					✓		✓		✓		✓		✓		✓														
	Control arm: conventional care						✓		✓		✓		✓		✓		✓		✓		✓		✓		✓		✓		✓		
**Assessments**																															
	Sociodemographic questionnaire		✓																												
	Primary outcome: 6MWT^a^ distance				✓														✓										✓		
	**Secondary outcomes**																														
		Spirometry^b^			✓														✓										✓		
		Respiratory symptoms (SGRQ^c^)			✓														✓										✓		
		Quality of life (SF-36^d^, EQ-5D^e^)			✓														✓										✓		
		Mental health (PHQ-9^f^, GAD-7^g^, IES-R^h^)			✓				✓				✓						✓		✓								✓		
		Cognitive function (MoCA-BLIND^i,^ visual impairment)			✓				✓				✓						✓		✓								✓		

^a^6MWT: 6-minute walk test.

^b^Includes forced expiratory volume in 1 second (FEV1), forced vital capacity (FVC), and FEV1/FVC ratio.

^c^SGRQ: Saint George’s Respiratory Questionnaire.

^d^SF-36: 36-Item Short Form Survey.

^e^EQ-5D: EuroQuol 5D.

^f^PHQ-9: Nine-Item Patient Health Questionnaire.

^g^GAD-7: Generalized Anxiety and Depression.

^h^IES-R: Impact of Event Scale-Revised.

^i^MoCA-BLIND: Montreal Cognitive Assessment visual impairment version.

### Comparison Groups

#### Intervention Arm

The intervention consisted of 12 sessions of home-based respiratory rehabilitation and 6 sessions of weekly psychological support delivered through telephone home calls throughout a period of 6 weeks. Participants began the rehabilitation program no later than 1 week after hospital discharge.

Respiratory rehabilitation consisted of 12 sessions (1-3 per week depending on the participant’s availability) performed at home under trained physiotherapist guidance. Each respiratory rehabilitation session lasted approximately 1 hour. In the first rehabilitation session, the physiotherapist brought the necessary equipment to perform the exercises (1-kilogram abdominal weight and a small rubber ball). In each session, the participant performed the following exercises: respiratory muscle training by breathing through pursed lips and breathing education exercises, coughing exercises to produce effective coughs, diaphragm training by teaching diaphragmatic contractions in the supine position with a light weight placed on the anterior abdominal wall, and stretching exercises whereby the participant was placed in a supine or lateral position with the knees bent to correct for lumbar lordosis. In addition, participants performed arm movements in flexion, horizontal extension, abduction, and external rotation. Participants were instructed to perform pursed-lip breathing and effective coughing on the days they did not receive assisted therapy, with a frequency of 30 times per day. The day of nonattendance at respiratory therapy was recorded. Given the risk of exposure to COVID-19, physiotherapists followed a strict biosafety protocol involving the use of personal protective equipment and a thorough disinfection process at each visit. In addition, rehabilitation was ideally performed in a well-ventilated room and the participant wore a surgical mask during visits as an extra protective measure.

The psychological support intervention consisted of an introductory session (Session 0) and 6 1-hour structured sessions based on emotion-centered problem-solving therapy (EC-PST). A trained licensed psychologist provided these sessions once a week by telephone home calls following the guidelines of the Inter-Agency Standing Committee (IASC) on Mental Health and Psychosocial Support in Humanitarian and Disaster Emergencies of the World Health Organization [18]. The EC-PST is an update of the classic problem-solving therapy that emphasizes guiding patients to better understand and manage their emotional reactions to stressful events as a means of coping with the negative effects of these stressors [19]. EC-PST reviews four components: (1) Planful Problem Solving, (2) Overcoming Brain Overload, (3) Enhancing Motivation for Action, and (4) Stop and Slow Down. In addition, we provided each participant with a printed workbook that included the themes and topics that were developed in each session, and the psychologist recorded the main points of the session using an adhoc evaluation form. Table 2 summarizes the objectives of each session.

**Table 2 table2:** Psychological support objectives.

Session	Content	Objectives
0	Introductory session and psychological history	Take the participant’s psychological medical history; evaluate stressful events, consequences, and the participant’s perception of what they are experiencing, through the functional behavioral analysis
1	Psychoeducation session	Provide information on the types of problem orientation and problem-solving styles; identify the problem-solving style employed by the patient
2	Toolbox training 1 “Stop and Slow Down”	Teach the “Stop and Slow Down” tool to better modulate emotional reactions to stressful stimuli. Strategies included are counting, guided imagery or visualization, deep breathing, “fake” yawning, conscious meditation, relaxation exercises, deep-muscle exercise or conscious walking, talking to someone, prayer, and the DAPA^a^ Method for Emotional Regulation
3	Toolbox training 2 “Overcome Brain Overload” and “Boost Motivation to Act”	Teach “Beat Brain Overload” tools to overcome barriers or obstacles to effective problem-solving, particularly when under stress, through three specific strategies: externalization, visualization, and simplification; orienting people to overcome low motivation and feelings of hopelessness through use of the “Power Motivation to Act” tool through externalization and visualization
4	Toolbox training 3 “Plan the Solution to Your Problems”	Explain and teach the four effective problem-solving steps: define the problem, generate solution alternatives, make the decision, and implement and verify the solution
5	Guided practice	Assist participants in adjusting the problem-solving skills they have acquired; monitor the application of these principles; help participants meaningfully integrate the various tools; reinforce the participant’s progress as a means to further increase the sense of self-efficacy
6	Prognosis assessment and termination of the psychological therapy	Prognosis assessment: discuss possible difficulties that the participant may have to help them plan their actions; evaluate the possibility of using the tools taught in the possibility of managing these difficulties. Therapy termination: review the EC-PST^b^ objectives established in the initial sessions; ask the patient for examples of how these objectives have been met

^a^DAPA: Dementia and Physical Activity: stop, walk slowly, think, act.

^b^EC-PST: emotion-centered problem-solving therapy.

#### Control Arm

Participants assigned to the control arm received posthospital usual care delivered by a Peruvian public hospital consisting of discharge recommendations and a telephone follow-up for 14 days provided by the same hospital. Although there are no national guidelines for standardized discharge indications in Peru, many hospitals recommended patients to perform home breathing exercises and symptomatic respiratory treatment. There are currently no diagnostic or follow-up plans for patients that experience or develop mental illness or a strategy for respiratory or psychological rehabilitation in most hospitals in Peru. We collected data about any additional nonstudy therapies that participants may have received from any internal or external health care provider.

### Measured Outcomes

#### Primary Outcome

The primary health outcome was the change in 6-minute walk distance (6MWD) at 7 and 12 weeks after discharge compared to baseline. The 6MWT is a submaximal effort test of cardiorespiratory functional capacity with correlation to QoL and independence in activities of daily living [20]. The 6MWT is widely used for the follow-up of patients after hospitalization because patients can self-regulate the intensity of the activity, resting as often as desired, leading to minimal risks of adverse events during the activity [20]. The test was performed in a 20-meter hospital aisle marked according to the recommendations of the American Thoracic Society [21,22]. Participants who demonstrated instability while standing, generalized weakness, or those with a decrease in oxygen saturation below 90% or increased heart rate of >130 beats per minute while standing did not perform the test. In this case, the participants were considered to have covered 0 meters. Each participant only attempted the test once. The number of meters walked in the 6MWT was calculated by the assessor and recorded in the data collection form.

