### Statistical Analyses

We will perform an intention-to-treat analysis of primary and secondary outcomes at 7 and 12 weeks after hospital discharge. The final analysis will be performed when all 108 participants completed the trial. We will compare the 6MWD (meters), FVC (liters), FEV1 (liters), and questionnaire scores at 7 and 12 weeks after hospitalization discharge between the intervention and control arms. In the secondary analyses, we will compare the proportion of participants with respect to restrictive spirometry pattern, depression, anxiety, and posttraumatic stress disorder at 7 and 12 weeks after hospital discharge between the intervention and control arms. In addition, following the recommendation by Cocks and Torgerson [32], we will use a one-sided 80% CI to determine if this trial should proceed to a phase III trial. As a sensitivity analysis, the association between the number of therapies received and outcomes will be examined, adjusting for potential confounders that will be identified by a causal acyclic diagram. There will be no formal interim analysis of the data.

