### Sample Size Calculation

We used STATA Version 16 (StataCorp) to calculate the ideal sample size. We attempted to enroll 108 participants in total, allocating 54 to each treatment arm. We estimate that a sample size of 86 participants would be sufficient to detect a mean difference between arms of 55.1 meters in the 6MWT according to the study by Liu et al [11] considering a 95% CI and 90% power. Assuming a potential 20% rate of rejection or loss to follow-up, we aimed to achieve a sample of 108 participants.

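### The primary outcome is set at both week 7 and week 12 with no rule for combining them, while the sample size covers one comparison; under the two plainest readings either the error rate or the power is not as planned

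*Protocol article*

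**What the plan says.** Three sections of the protocol article give the primary comparison two time points.

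- Primary Outcome: "The primary health outcome was the change in 6-minute walk distance (6MWD) at 7 and 12 weeks after discharge compared to baseline".
- Introduction, last paragraph: "The primary objective of the trial was to compare 6-minute walking distances at 7 and 12 weeks after hospital discharge".
- Statistical Analyses: "We will perform an intention-to-treat analysis of primary and secondary outcomes at 7 and 12 weeks after hospital discharge".

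Table 1 schedules the walk test at baseline, week 7 and week 12. None of these places ranks the two follow-up visits, gives a joint or averaged contrast, sets a testing order, or says whether one success is enough or two are needed.

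The Sample Size Calculation section works with a single difference, "sufficient to detect a mean difference between arms of 55.1 meters in the 6MWT", "considering a 95% CI and 90% power". It names no visit. It arrives at 86 evaluable participants and inflates this: "Assuming a potential 20% rate of rejection or loss to follow-up, we aimed to achieve a sample of 108 participants".

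**The concern.** Two primary comparisons are declared and one is sized. The visits also ask different questions. The programme lasts 6 weeks and starts within a week of discharge, so week 7 is the first walk test after it ends and week 12 comes five weeks later. One measures the immediate effect and the other its persistence, so the results could differ.

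Three things are then at stake:

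- If either visit can carry the claim and each is tested at 5%, the chance of a false positive primary result exceeds 5%.
- If both must succeed, power is below the 90% used for sizing.
- If the visits disagree, the plan has no defined primary answer, and a choice made after seeing the results would be selective.

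The one-sided 80% CI rule for going on to phase III, in Statistical Analyses, names no visit either.

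**Working it through.** **Inputs from the protocol article (Sample Size Calculation).** Difference 55.1 m; 95% CI, read here as two-sided 5% because sidedness is not written; power 90%; 86 evaluable, 43 per arm; 20% loss; 108 enrolled, 54 per arm.

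**Assumptions.** The SD is not given, so it is back-solved. The correlation r between the two visits' test statistics is not given either, so a range is shown. For power, the true difference is 55.1 m at both visits, with equal SDs. A normal approximation is used throughout.

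**1. The plan's own figures.** Enrolment: 86 / (1 − 0.20) = 107.5, rounded up to 108, as stated. The 86 cannot be reproduced independently without an SD. From n per arm = 2·SD²·(z₀.₉₇₅ + z₀.₉₀)² / 55.1², n = 43 implies SD ≈ 78.8 m (about 77.9 m with a t test). So 86 fits one two-arm comparison. The expected test statistic is 55.1 / (78.8·√(2/43)) = 3.242, and power is Φ(3.242 − 1.960) = 0.900.

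**2. Win at either visit, 5% each.** Type I error = P(|Z₁| > 1.96 or |Z₂| > 1.96), with Z₁ and Z₂ bivariate normal, means 0, correlation r. For r = 0 this is 1 − 0.95² = 0.0975.

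**3. Both visits required, 5% each.** Error stays at or below 5%. Power = P(Z₁ > 1.96 and Z₂ > 1.96) with both means 3.242. For r = 0 this is about 0.90² = 0.81.

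**4. Bonferroni, 2.5% each, win at either visit.** The critical value is 2.241. Power at a single visit is Φ(3.242 − 2.241) = 0.84. Trial-level power is the probability of crossing at one visit or more.

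**5. One contrast averaging the visits, 5%.** The expected statistic becomes 3.242 / √((1 + r)/2). For r = 0.5 it is 3.744, so power is Φ(1.784) = 0.963. For r = 0.8 it is 3.417, so power is Φ(1.457) = 0.927.

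| r | Error, either visit at 5% | Power, both required | Power, Bonferroni, either visit | Power, averaged contrast |
|---|---|---|---|---|
| 0.5 | 9.1% | 83.3% | 93.8% | 96.3% |
| 0.7 | 8.35% | 84.7% | 91.6% | not run |
| 0.8 | 7.8% | 85.6% | 90.2% | 92.7% |
| 0.9 | 7.0% | 86.9% | 88.5% | 91.4% |

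The error column does not depend on the SD. The power columns depend on it only through the stated 90% for a single test.

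**6. Size needed if both visits are required.** Joint power of 90% needs 48 per arm at r = 0.9 and 53 at r = 0. That is 96 to 106 evaluable and 120 to 133 enrolled (96/0.80 = 120; 106/0.80 = 132.5, rounded up).

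**7. The 80% CI rule.** If it were applied at both visits with a win at either, its error could reach 1 − 0.80² = 36% for independent visits.

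**The case against.** The strongest reply is that the plan leaves a rule unstated rather than giving a wrong figure. A reader might infer that either the 5% or the 90% must be false whatever rule is used. The documents do not support that. An averaged contrast keeps both figures at every correlation in the table, and Bonferroni with a win at either visit keeps both up to a correlation of about 0.8. It would also be wrong to say that Bonferroni costs the trial six points of power: 84% is the power at one visit, while trial-level power is 90% to 94% at correlations of 0.8 to 0.5. The 5% itself is inferred from the 95% CI.

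The second reply is that a journal article may leave the test, the longitudinal model and the multiplicity method to an analysis plan that is not shown. That is fair for those details, and a repeated-measures analysis would be compatible with the text. It does not answer the point in full. The article is not silent on timing: it fixes two primary time points in the objective, the outcome and the analysis, and then sizes for one difference. An unseen plan that chose one visit would conflict with that published text.

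The third reply concerns timing and choice of visit. The abstract puts recruitment and data collection between October 2020 and June 2021, and Study Design says that only the data analyst was blinded. A rule chosen now is therefore a late change by people who were not all blinded. This stands and shapes the fix. It also stands that the documents give the visits equal standing, so the sample size does not favour week 7 over week 12.

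**Conclusion.** The point holds in conditional form. The article declares two primary time points, gives no rule for combining them and sizes one comparison. Under a win at either visit at 5% each, the type I error is about 7.8% to 9.1% for correlations of 0.8 to 0.5, and 9.75% if the visits are independent. Under a requirement for both, power is about 83% to 86% over the same correlations. These figures assume a two-sided 5% test, the assumed correlations and, for power, a true 55.1 m at both visits.

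The article does not show which rule the investigators intend, so the inflated error is not established as the trial's actual error rate, nor is 86 shown to be the wrong number. What is established is that neither the error rate nor the power is secured until a rule is stated.

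**What to change.** Fix one rule in a dated amendment before the blinded analyst sees results by arm, and disclose in the trial report that it was set after data collection. Any of these would do:

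- **One primary visit.** Test it at 5%, and test the other at 5% only if the first is significant. Week 7, the first visit after the programme, is one reasonable choice; week 12 would also fit the sample size. The Introduction and Primary Outcome wording should change to match.
- **Both visits in one contrast.** Average the two between-arm differences in a repeated-measures analysis, tested once at 5%.
- **Both visits with Bonferroni.** Test each at 2.5%, with a win at either.

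The sample size section should then state which comparison it covers. With 55.1 m at each visit tested, 86 evaluable and 108 enrolled can stand under all three; Bonferroni also needs a correlation of about 0.8 or less. The one-sided 80% CI rule should be tied to the same visit or contrast.

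The cost is mainly wording and disclosure. With a named visit, the other can no longer carry the trial alone. An averaged contrast gives one answer and does not separate the immediate effect from its persistence. Under any option, the late choice must be reported as such.

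### The 0 m score for an unperformed walk test is not limited to any visit; if it was used at baseline, a change-from-baseline primary outcome is fragile, and a baseline-adjusted comparison avoids this

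*Protocol article*

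**What the plan says.** Under Primary Outcome, the article lists signs seen on standing that stop the walk test: instability, generalized weakness, or "a decrease in oxygen saturation below 90% or increased heart rate of >130 beats per minute while standing did not perform the test". It then gives the score: "In this case, the participants were considered to have covered 0 meters". No visit is named.

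The same section defines the outcome as a change: "The primary health outcome was the change in 6-minute walk distance (6MWD) at 7 and 12 weeks after discharge compared to baseline". Statistical Analyses describes a comparison of levels: "We will compare the 6MWD (meters), FVC (liters), FEV1 (liters), and questionnaire scores at 7 and 12 weeks after hospitalization discharge". It mentions neither a change score nor adjustment for baseline.

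Two other places bear on who could have a 0 m baseline. The exclusion criteria in Textbox 1 rule out people for whom the walk test is contraindicated (the contraindications are not listed) and people who had complications during the baseline test. The Enrollment section says: "Patients who completed the baseline assessments and met eligibility criteria were enrolled into the study". Those assessments include the walk test.

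Sample Size Calculation states that "a sample size of 86 participants would be sufficient to detect a mean difference between arms of 55.1 meters in the 6MWT", with a 95% CI and 90% power. It gives no SD and no allowance for zero scores.

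**The concern.** A test that was withheld enters a metre-scale outcome as if a distance had been measured. At follow-up, this can be read as a deliberate worst-case score. At baseline under a change score it does something else: the person's entire follow-up distance becomes improvement, whichever arm they are in. A few such people add a large variance component unrelated to treatment, and a chance imbalance of one or two between arms moves the estimated effect noticeably.

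The situation is plausible. Baseline was taken around discharge, in people who had needed more than 6 L/min of oxygen. The trial was also open-label, and some of the triggers (instability, generalized weakness) are judgements, each of which can change a score by the whole distance a person would have walked. Adequate power is named under Strengths and Limitations as the trial's main strength, so a loss of power bears on a stated claim.

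**Working it through.** **1. Reproducing the plan's sample size.** Stated inputs: difference 55.1 m, 86 evaluable (43 per arm), 90% power, and a 95% CI taken as two-sided alpha 0.05. The SD is not stated, so 86 cannot be reproduced directly. Solving for the SD:

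- Normal approximation: SD = 55.1 / [(1.960 + 1.282) × √(2/43)] = 78.8 m.
- t-test: SD = 77.9 m.

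The inflation for loss does reproduce: 86 / 0.80 = 107.5, rounded up to 108. I use 77.9 m below as an implied value.

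**2. Can a 0 m baseline occur?** Set side by side:

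- Primary Outcome: failing the standing check means no test and a score of 0 m, at an unspecified visit.
- Textbox 1: excludes contraindications (unlisted) and complications during the baseline test. Someone who never starts the test has no complication during it, and the standing signs are not called contraindications.
- Enrollment: requires completed baseline assessments. Whether an assigned 0 m counts as completed is not said.

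The text allows either reading.

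**3. Effect of baseline zeros on a change score.** Further assumptions: baseline walkers' mean 300 m, correlation 0.5 between baseline and follow-up, the same share p of baseline zeros in each arm, and 55.1 m effect at follow-up. With equal SDs and correlation 0.5, the change-score SD without zeros is 77.9 × √(2 × (1 − 0.5)) = 77.9 m. With zeros:

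SD of change = √[77.9² + p(1 − p) × 300²]

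- p = 5%: √(6,068 + 4,275) = 101.7 m. Power: 55.1 / (101.7 × 0.2157) − 1.96 = 0.55, or about 71%.
- p = 10%: √(6,068 + 8,100) = 119.0 m. Power: 55.1 / (119.0 × 0.2157) − 1.96 = 0.19, or about 57%.

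Simulation gives about 70% at 5% zeros and 55% to 57% at 10%.

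One extra baseline zero in one arm shifts that arm's mean change by 300 / 43 = 7.0 m, and 7.0 / 55.1 = 13% of the target difference. At a mean of 200 m the shift is 4.7 m; at 400 m it is 9.3 m.

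**4. Alternatives on the same assumptions (simulated power).**

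| Analysis | No zeros | 5% baseline zeros | 10% baseline zeros |
|---|---|---|---|
| Change score | about 90% | about 70% | 55–57% |
| Follow-up distance, unadjusted | about 90% | 90–91% | about 90% |
| Follow-up adjusted for baseline | 96–97% | 93–94% | 92–93% |
| Same, plus not-testable indicator | 96–97% | about 96% | 95–96% |

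Most of the gain over the change score comes from ordinary baseline adjustment. The indicator adds about 2 to 4 points.

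**5. Follow-up zeros.** Take 5% zeros in both arms and control walkers averaging 400 m, using an SD of 78 m. The mixture variance in an arm is (1 − p) × SD² + p(1 − p) × mean². The control SD is 115.7 m and the intervention SD (mean 455.1 m) is 125.0 m, so the pooled SD is 120.4 m. The difference in means becomes 0.95 × 55.1 = 52.3 m, and t-test power is about 52%. A rank test keeps about 81%. With 5% zeros in control but 2% in the intervention arm, t-test power is about 81%.

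**The case against.** The other side has several good points.

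- **The passages may be consistent.** A reader might infer that the 0 m rule contradicts the exclusion criteria. The documents do not show that. The Enrollment condition may have kept out everyone who could not start the test, in which case the rule acts only at follow-up and no baseline zero exists. What stands is that the passages are not reconciled.
- **Scoring inability as 0 is legitimate.** A reader might infer that it invalidates a comparison of means. With randomization and even application, it is a defined composite and the difference in means is valid. It is less precise, and it mixes ability to do the test with distance walked.
- **No planned SD is exceeded.** None is stated. The 77.9 m is back-solved, and whether the cited study's SD already included zeros cannot be seen here.
- **Large artificial gains are conditional.** They need people enrolled at 0 m and an analysis of change. Under the comparison of follow-up distances described in Statistical Analyses, baseline zeros cost no power (table above). But the outcome is defined as change in another section, so that protection is not secured.
- **Follow-up power loss is one scenario.** It assumes that treatment does not affect inability to walk. If rehabilitation reduces inability, zeros carry signal and much of the power returns, as the 5% against 2% case shows.
- **A rank test should not be triggered by the data.** Moving the primary p-value to ranks once a zero is seen would let the observed data choose the test and would detach it from the metre effect used for sample size. This objection holds in full, so ranks belong in a sensitivity analysis fixed beforehand.

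**Conclusion.** The point holds in a limited form. The 0 m rule has no stated visit, the primary outcome is defined as change, and the documents leave open whether people untestable at baseline were enrolled. If none were, the baseline problem disappears. If 5% to 10% were, a change score would have about 70% to 55% power in place of about 90%, and each extra zero in an arm would move its mean change by about 7 m. These figures rest on 43 per arm, a back-solved SD of 77.9 m, a baseline mean of 300 m, a correlation of 0.5 and assumed zero rates; the document gives no walking distances or zero counts. The follow-up loss is real but more dependent on assumption and is secondary. The clinical thresholds for withholding the test are not judged here.

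**What to change.** 1. State at which visits the 0 m rule applied, and reconcile Primary Outcome, Textbox 1 and Enrollment on whether people untestable at baseline were enrolled.
2. Define the primary analysis as walk distance at weeks 7 and 12 compared between arms with adjustment for baseline walk distance, not as a change score. If baseline zeros exist, add an indicator for not testable at baseline.
3. Report the number scored 0 m by arm and visit.
4. Specify in advance, whether or not zeros are seen, a rank-based baseline-adjusted sensitivity analysis with untestable participants ranked worst. An observed zero must not switch the primary test.

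The cost is revised wording and a little more analysis. All the data needed are already collected. If no baseline zeros occurred, the indicator drops out and the baseline adjustment still raises power under the assumptions above.
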